	**Follow-up**	
	• Starts at the randomization (assignment of a strategy, just before dialysis initiation) • Ends at death, informative censoring due to a competing event (kidney transplantation, recovery of kidney function, withdrawal from dialysis), administrative censoring (end of study or after 5 years) or loss-to-follow-up, whichever came first.	• Starts at the emulated randomization (assignment of a strategy, just before dialysis initiation, or within 14 days after initiation*) • Ends at death, informative censoring due to a competing event (kidney transplantation, recovery of kidney function, withdrawal from dialysis), administrative censoring (31 December 2024 or after maximum follow-up^♠^) or loss-to-follow-up, whichever came first.

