### Outcomes

The primary outcome will be the cumulative incidence of all-cause mortality. Secondary outcomes will be cardiovascular mortality, infection-related mortality including COVID-19 and infection-related mortality excluding COVID-19. Additionally, all-cause hospitalization and cause-specific hospitalization, as well as the length of hospitalization (proportion of the follow-up time in days) will be analyzed. Standard International Classification of Diseases (ICD-10) codes will be used to determine these outcomes. ICD-10 codes that are used to determine the outcomes are summarized in Supplemental Table S2. Lastly, the dose-relationship between convection volume and outcomes will be investigated for patients receiving HDF, with convection volume analyzed as a continuous variable to preserve all information that would otherwise be lost through categorization.

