#### CCW approach

First, a stacked dataset will be created in which each individual is duplicated, creating one clone for each of the two treatment strategies. As a result, both treatment groups will be perfectly balanced at baseline. However, selection bias may arise after baseline because clones are followed over time and artificially censored when their observed data deviates from the assigned treatment strategy. Of course, patients can be censored both within the grace period and after the grace period due to competing risks, including kidney transplantation, recovery of kidney function or dialysis withdrawal. Both forms of censoring are likely to be informative. To address this issue, we will apply inverse-probability-of-censoring weighting (IPCW) using a generalized linear model (GLM) that includes covariates predictive of censoring and the outcome. We will determine weights for the grace period and the period thereafter separately. Weighting within the grace period will take place every two weeks, whereas weighting for the period after that will occur with yearly intervals. The probability of remaining uncensored will be the outcome of this model. To assess whether the weights adequately reduce covariate imbalance between the two arms due to artificial censoring during the grace period, we will calculate the standardized mean difference (SMD). A SMD above 10% will be considered evidence of residual imbalance, potentially indicating misspecification of the weight model [16]. The weighting approaches with the included covariates in each model of both CCW and MSM are summarized in Fig. 1.

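### Follow-up is censored at dialysis withdrawal as a competing event, so deaths after withdrawal drop out of a primary outcome labelled all-cause mortality

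*Protocol article*

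**What the plan says.** The Outcomes section states: "The primary outcome will be the cumulative incidence of all-cause mortality". The secondary outcomes are cause-specific: "Secondary outcomes will be cardiovascular mortality, infection-related mortality including COVID-19 and infection-related mortality excluding COVID-19".

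In Table 1, Follow-up, both the target-trial and the emulation columns give the same end-of-follow-up rule: "Ends at death, informative censoring due to a competing event (kidney transplantation, recovery of kidney function, withdrawal from dialysis"), then administrative censoring "or loss-to-follow-up, whichever came first". The CCW approach section repeats that patients may be censored, within and after the grace period, "due to competing risks, including kidney transplantation, recovery of kidney function or dialysis withdrawal".

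On handling, that section says "Both forms of censoring are likely to be informative" and applies IPCW. Weights are two-weekly in the grace period, and "weighting for the period after that will occur with yearly intervals". The marginal structural model (MSM) uses IPCW at 6-month intervals. No section says that a death after withdrawal is counted, and none says how such deaths are recorded. The abstract says that competing risk bias is controlled.

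**The concern.** A competing event is one after which the outcome can no longer occur. Withdrawal from dialysis leaves death possible and, in a patient who depends on dialysis, makes it more likely. Under a first-event rule, a patient who stops dialysis and then dies enters the primary analysis as a censored observation. The outcome is then mortality while on dialysis, not all-cause mortality.

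IPCW cannot put these deaths back. It gives more weight to comparable patients who stay on dialysis, so it estimates the risk in a hypothetical setting where nobody withdraws. Such an estimand can be chosen, but the article does not choose it. The stated aim is the effect in routine clinical practice, where patients do withdraw.

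Absolute mortality and restricted mean survival time are at stake in both arms. The hazard ratio is also at stake if HDF affects withdrawal-related deaths differently from other deaths.

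**Working it through.** **Reading the sections together**

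1. Table 1 gives the target trial an intention-to-treat effect, but its analysis row refers back to the Follow-up row for censoring, which stops at withdrawal. An intention-to-treat analysis of all-cause mortality would keep following the patient. The mismatch therefore sits in the target trial itself and is not only a data limitation of the emulation.
2. Interpretation and estimands says that, for CCW, adherence matters only in the 90-day grace period, whatever happens to treatment afterwards. A later withdrawal is not a departure from either strategy, so the per-protocol estimand does not require censoring there.
3. Even the no-withdrawal estimand needs measured predictors of withdrawal. The Discussion says that functional status was not systematically registered and could not be included. After day 90 the CCW weights change only yearly.

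**Illustration of absolute risk**

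The article states no event rate, so there is no figure to reproduce. Inputs:
- T = 4.75 years, the maximum follow-up in the Table 1 footnote.
- Total death hazard h = 0.14 per year (assumed).
- Share w of deaths that follow withdrawal = 10-30% (assumed).
- Hazards constant, and death soon after withdrawal (assumed).

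All deaths counted: 1 - exp(-hT) = 1 - exp(-0.665) = 48.6%.

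Censored at withdrawal: 1 - exp(-hT(1 - w)).

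| w | Exponent | Reported risk |
|---|---|---|
| 10% | 0.665 × 0.9 = 0.5985 | 45.0% |
| 20% | 0.665 × 0.8 = 0.5320 | 41.3% |
| 30% | 0.665 × 0.7 = 0.4655 | 37.2% |

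A second set of assumptions used on-dialysis death rates of 0.08-0.16 per year and withdrawal rates of 0.005-0.04 per year. The share of deaths dropped, withdrawal rate / (death rate + withdrawal rate), runs from 0.005/0.165 = 3% to 0.04/0.12 = 33%. The 4.75-year risk is understated by about 1 to 12 percentage points. At 0.12 and 0.02 it is 43.4% instead of 48.6%.

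**Illustration of the hazard ratio**

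Assume a hazard ratio of 0.77 on other deaths and r on withdrawal-related deaths, with w the share in the comparator arm. The all-cause hazard ratio is (1 - w) × 0.77 + w × r. The censored analysis reports 0.77 throughout.

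| r | w = 10% | w = 30% |
|---|---|---|
| 0.70 | 0.693 + 0.070 = 0.763 | 0.539 + 0.210 = 0.749 |
| 0.77 | 0.770 | 0.770 |
| 1.00 | 0.693 + 0.100 = 0.793 | 0.539 + 0.300 = 0.839 |
| 1.30 | 0.693 + 0.130 = 0.823 | 0.539 + 0.390 = 0.929 |

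The bias is zero when r = 0.77 and changes sign around it.

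**Secondary point, cause-specific mortality**

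Assume cardiovascular and other-cause death rates of 0.05 and 0.07 per year. If other-cause death were censored, the reported risk would be 1 - exp(-0.05 × 4.75) = 21.1%. The cumulative incidence is (0.05/0.12) × (1 - exp(-0.12 × 4.75)) = 18.1%. The ratio is 1.17. Splits of 0.06/0.06 and 0.03/0.09 give 1.14 and 1.22.

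**The case against.** The best defence is that the rule is open. Table 1 states it for the target trial and carries it into the emulation. For the MSM, which concerns sustained treatment over the whole period, stopping dialysis could be seen as leaving the strategy, so censoring there has some logic. The data may also not allow more. They come from one provider, and Datasource describes hospital deaths as registered during the dialysis course, so deaths after that course may be missing. If withdrawal deaths are coded simply as deaths, fewer or none are lost. These points stand as limits on size and feasibility. They do not make withdrawal a competing event for death, and they do not declare the no-withdrawal estimand.

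Four stronger readings are tempting but not supported:

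- *The plan favours HDF.* The direction depends on how HDF acts on withdrawal-related deaths, and the documents do not say.
- *Other-cause death is plainly censored.* The article does not state the cause-specific estimator. Death of any cause ends follow-up, and the list in the CCW section is introduced as non-exhaustive. A fuller plan could settle this.
- *Loss to follow-up gets no weight.* Table 1 lists it apart from informative censoring, but no section says it is left out of the weights.
- *One censoring model for transplantation and withdrawal hides their opposite predictors.* An IPCW weight depends on the total censoring hazard, so opposing effects that cancel there are no error in themselves. The models are set out in Fig. 1, which is not available here.

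**Conclusion.** The point holds for the primary outcome. Two sections expressly end follow-up at withdrawal, and none counts a later death, so the outcome as defined is narrower than its label. The resulting estimand is undeclared and conflicts with the routine-practice aim and the intention-to-treat target trial.

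The documents fix neither the size nor the direction of any hazard ratio bias. The fall from 49% to about 45-37% is an illustration that rests on the assumed hazard, the assumed share and prompt death after withdrawal. The actual effect also depends on how withdrawal deaths are recorded. The cause-specific point is secondary: it asks for a statement that would support the abstract's claim about competing risks, and it does not identify a stated error.

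**What to change.** 1. For all-cause mortality, do not censor at withdrawal in either the CCW or the MSM analysis. Count recorded deaths after withdrawal as events.
2. Where later death is not recorded, use a death-or-withdrawal composite, applied identically in both arms. State how withdrawal and subsequent death are coded in the database.
3. Keep the present censoring rule as a sensitivity analysis, labelled as the hypothetical no-withdrawal estimand.
4. Change Table 1 (both columns) and the CCW text so that withdrawal is no longer called a competing event for death.
5. State that the cumulative incidence of cardiovascular and infection-related mortality will be estimated with other-cause death as a competing event.

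The cost is revised wording and modest extra modelling. The main drawback is that the composite misclassifies any patient who survives withdrawal, which is a further reason to report the sensitivity analysis beside it.

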**HDF strategy:**

Initiate HDF within the first 90 days after dialysis initiation (grace period).Continue HDF throughout the grace period (receiving at least three HDF treatments every two weeks).

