### Interpretation and estimands

Both the CCW approach and MSM aim to estimate the average treatment effect (ATE) to quantify the causal effect of treatment strategies in the target population. However, the CCW approach compares the effect of initiating HDF within 90 days with not initiating HDF within 90 days, whereas the MSM compares the effect of sustained treatment with HDF versus sustained treatment with HD over the entire study period. In the CCW framework, treatment adherence is assessed during the predefined grace period, requiring full adherence to the assigned strategy within this window, irrespective of treatment changes thereafter.

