**Example ID 4 Fig5:**
[figure not shown]
The clone assigned to HDF will be censored because the individual has started HDF, but not continued HDF for three times within each consecutive two week period within the grace period. The clone assigned to HD will be censored because the individual has started HD, but not continued HD more than three times within each consective two week period within the grace period

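### The stated check of the clone-censor weights compares the two arms only with each other, so it cannot detect both arms drifting away from the eligible cohort in the same direction

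*Protocol article*

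**What the plan says.** The section CCW approach creates two clones per patient and notes the consequence: "As a result, both treatment groups will be perfectly balanced at baseline". It recognises that later censoring, both artificial and through competing events, is likely to be informative. It therefore prescribes inverse-probability-of-censoring weights from a generalized linear model, updated every two weeks in the grace period. One diagnostic for these weights is stated, an SMD. Its purpose is: "To assess whether the weights adequately reduce covariate imbalance between the two arms due to artificial censoring during the grace period". Its limit is: "A SMD above 10% will be considered evidence of residual imbalance, potentially indicating misspecification of the weight model".

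The section Interpretation and estimands says that both analysis methods "aim to estimate the average treatment effect (ATE) to quantify the causal effect of treatment strategies in the target population".

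Example ID 4 of Fig. 2 shows one patient losing both clones. For one clone: "The clone assigned to HDF will be censored because the individual has started HDF, but not continued HDF for three times". For the other: "The clone assigned to HD will be censored because the individual has started HD, but not continued HD more than three times".

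The article's other weight diagnostic, a look at the weight distribution for extreme values, stands under Marginal structural model and does not compare an arm with the cohort either.

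**The concern.** In a cloned design the target of the weights is known at time zero: each weighted arm should again look like the whole eligible cohort. Comparing the arms with each other tests only whether they resemble one another. If the weight model misses a feature of patients who leave both arms, both arms shift in the same direction, their SMD stays near zero and the 10% limit is not triggered.

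Two routes out of both arms are in the plan. Patients who sustain neither modality in the grace period lose both clones. Transplantation, recovery of kidney function and withdrawal from dialysis end follow-up for whichever clones remain.

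At stake is the population that the results describe. The primary outcome is a cumulative incidence, restricted mean survival time (RMST) is also reported, and the study's rationale is that it represents routine practice better than the trials did. A common drift would make the absolute results describe a different group from the eligible cohort, with no warning from the stated check.

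**Working it through.** The article gives no figure to reproduce here. It states neither the share of patients who lose both clones nor how they differ from the rest, so both are assumed below and varied.

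**1. Who loses both clones.** The rules are at least three HDF sessions, or more than three HD sessions, per two weeks.
- Six sessions delivered: three or more HDF meets the HDF rule, and two or fewer HDF means four or more HD, which meets the HD rule. Exactly one strategy is always met.
- Five sessions: neither is met with 2 HDF + 3 HD.
- Four sessions: neither with 1 + 3 or 2 + 2.
- Three sessions: neither with 0 + 3, 1 + 2 or 2 + 1.

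Across windows, a patient who moves once from HD to HDF and stays keeps the HDF clone. Both clones are lost when both modalities are started and neither is kept up, as in Example ID 4.

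**2. Why this group matters.** If every patient stayed in exactly one arm, with share p in the HDF arm, then p × mean(HDF) + (1 − p) × mean(HD) = cohort mean. The unweighted departures of the two arms would then have opposite signs, and a between-arm SMD would show them. A shift in the same direction needs patients lost from both arms.

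**3. Size of an uncorrected shift.** Let a share q be lost from both arms, with mean d SD above the patients kept. Each arm then lies dq below the cohort mean, and the between-arm SMD is 0. Scaled by the cohort SD:

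SMD = dq / √(1 + q(1 − q)d²)

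For q = 0.2 and d = 0.6: 0.12 / √(1 + 0.16 × 0.36) = 0.12 / 1.028 = 0.117.

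Ignoring the small denominator, the shift passes 0.10 only if dq > 0.10. That needs d above 2 SD at q = 5%, 1.0 at 10%, 0.5 at 20% and 0.33 at 30%.

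**4. Effect on absolute risk.** Assume a hazard of 0.14 × exp(0.5z) per year, with z normal within each group. The 5-year risk is the mean of 1 − exp(−5 × hazard).

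| q | d | Arm-versus-cohort SMD | Between-arm SMD | Error in 5-year risk (points) |
|---|---|---|---|---|
| 0.1 | 0.4 | 0.04 | 0 | 0.6 |
| 0.2 | 0.4 | 0.08 | 0 | 1.3 |
| 0.2 | 0.6 | 0.12 | 0 | 2.0 (49.4% instead of 51.4%) |
| 0.3 | 0.8 | 0.23 | 0 | 3.9 |

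**5. Effect on the contrast.** Add an assumed hazard ratio of 0.8. For q = 0.2 and d = 0.6, the 5-year risk difference is 6.87 points in the drifted population against 6.95 in the full cohort. The RMST difference is about 81.5 against 84.1 days. Over q = 0.1 to 0.3 and d = 0.4 to 0.8, the error is at most 0.17 points in the risk difference and about 5 days in the RMST difference.

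**6. What weighting does.** A simulation used 200,000 patients, one measured covariate and logistic censoring weights fitted per arm.
- With 18% lost from both arms and a gap of 0.73 SD, the unweighted between-arm SMD was −0.007 and the arms differed from the cohort by −0.139 and −0.132. Weights linear in the covariate reduced these to −0.009 and −0.010.
- With 25% lost from both arms, a non-linear dependence of censoring on the covariate and linear weights, the share of patients with high covariate values had a between-arm SMD of 0.003, which passes. The arm-versus-cohort SMDs were −0.203 and −0.206, which both fail. Adding a squared term to the weight model roughly halved them, to −0.095 and −0.100.

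**The case against.** The strongest defence is that the between-arm SMD correctly checks what the article says it checks, and that a bias between arms is what would most mislead about HDF. Both parts stand: step 5 shows that a common drift barely moves the contrast. It is also fair that the article prescribes weights meant to remove this drift, and that adequate weights largely do. If the driver of censoring is unmeasured, an arm-versus-cohort SMD would miss it too. The article is condensed and Fig. 1 and the supplement are not shown, so this point concerns the diagnostic as the text fixes it, without claiming that no other exists.

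Three stronger readings are tempting and are not supported.
- A reader might infer that the drift is likely. The article says that switching is common, but not how many patients lose both clones or how they differ. In the range above, every scenario with 10% of patients stays below the 10% limit.
- A reader might infer that any switching patient loses both clones. Step 1 shows that a single lasting switch keeps one.
- A reader might infer that the estimated treatment effect would be badly wrong. The error lies mainly in the absolute results.

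The defence does not remove the gap. The SMD is there to reveal a misspecified weight model, and misspecification is the case in which the drift survives. Nor is this a detail left to a later document, since the article fixes the comparison and its limit.

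One caution applies to the remedy. The cohort is an exact reference only at time zero. By day 90 deaths have changed who is still under follow-up, so a comparison that ignores them would read mortality as censoring drift. At the figures assumed here that effect is small, about −0.02 SD.

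**Conclusion.** The point holds as a limitation of the stated check. A between-arm SMD cannot detect weight misspecification that moves both arms the same way, although the estimand refers to the population from which both arms were cloned. Drift of this kind is possible and would go unnoticed, and its size in this study is unknown. It exceeds 10% only if enough patients lose both clones, they differ enough, and the weights fail on a measured driver of their censoring. In the assumed case (20%, 0.6 SD, no correction by the weights, log-hazard 0.5 per SD, 0.14 deaths per year at the mean) the arm-versus-cohort SMD is 0.12 and 5-year risk is off by about 2 points. With an assumed hazard ratio of 0.8 the risk difference changes by about 0.1 point. The harm is to absolute cumulative incidence, RMST and the generalizability claim. This is a cheap improvement worth making and does not invalidate the comparison of HDF with HD.

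**What to change.** In the section CCW approach:
- Add the weighted SMD of each arm against the eligible cohort's baseline covariates, at each two-week step and immediately after the day-90 censoring. Count patients who die in the grace period at their last weight.
- Keep the between-arm SMD as a second check.
- Report the number and baseline profile of patients whose two clones are both censored.
- If either SMD exceeds 10%, respecify the weight model (for example with non-linear terms or interactions) before outcomes are examined.

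The covariates and weights already exist, so the cost is a little extra analysis work.

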**Fig. 1 Fig1:**
[figure not shown]
Weighting approach for Clone-Censor Weighting (CCW) and Marginal Structural Model (MSM). For the Clone-Censor-Weighting approach, weighting will take place every two weeks in the grace period of 90 days. Separate weights for artificial censoring for the treatment strategy, and for the informative censoring are calculated. Afterwards, weighting is repeated at the end of each year during the total follow-up of 5 years. For the Marginal Structural Model approach, weighting will take place every 6 months for the total follow-up of 5 years. Separate weights for treatment modality switches (IPTW) and for informative censoring are calculated. IPTW, inverse probability of treatment weighting; IPCW, inverse probability of censor weighting; Kt/V, metric for dialysis adequacy based on urea clearance (K), treatment time (t) and distribution volume (V); HbA1c, hemoglobin A1c

At two-weekly intervals, we will determine whether clones are adherent to their assigned treatment strategies. Of note, an event only contributes to the arm in which the patient is still uncensored at the time of event. For the HDF initiation strategy, patients will be censored at 90 days if they have not initiated HDF, and vice versa for the HD strategy. Individuals who die within the grace period while having received only one modality will have their replicated observations contribute follow-up time and a death event to both treatment strategies. This approach reflects the assumption that these early deaths could have occurred under either treatment strategy, as no clear modality choice had yet been established. By attributing these early events to both arms, this design prevents immortal time bias. Examples of censoring for the treatment strategies are shown in Fig. 2.

